### **2.2 Secondary Objectives (7/10/07)**

- 2.2.1 Determine freedom from PSA failure (*ASTRO consensus definition; See Endpoints, Section 13.0*), disease-specific survival, local progression, and distant metastases.
- 2.2.2 Collect dose/volume data to allow tumor control probability and normal tissue complication probability modeling for patients treated with radiation therapy for prostate cancer.
- 2.2.3 Determine the incidence of grade 2 or greater GU and GI acute and late toxicity in patients treated with each of the regimens described above.
- 2.2.4 Prospectively collect quality of life data, including sexual function, to compare outcomes between the two treatment groups.
- 2.2.5 Prospectively collect diagnostic biopsy samples to determine the influence of histopathologic or tumor-specific cytogenetic or chromosomal markers on cancer control outcomes following radiation.
- 2.2.6 To collect paraffin-embedded tissue blocks, serum, plasma, and buffy coat cells for future translational research analyses.

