#### **6.12 Radiation Toxicity (7/10/07) (3/29/10)**

- 6.12.1 All patients will be seen weekly by their radiation oncologist during radiation therapy. Any observations regarding radiation reactions will be recorded and should include attention toward the following potential side effects:
  - 6.12.1.1 Small bowel or rectal irritation manifesting as abdominal cramping, diarrhea, rectal urgency, proctitis, or hematochezia
  - 6.12.1.2 Bladder complications including urinary frequency/urgency, dysuria, hematuria, urinary tract infection, and incontinence
  - 6.12.1.3 Radiation dermatitis
- 6.12.2 Clinical discretion may be exercised to treat side effects from radiation therapy. Rectal side effects such as diarrhea may be treated with Diphenoxylate or Loperamide. Bladder or rectal spasms can be treated with anticholinergic or Tolterodine. Bladder irritation can be managed with Phenazopyridine. Erectile dysfunction can be treated with Sildenafil.
- 6.12.3 Acute toxicity monitoring: Acute ( $\leq 90$  days from RT start) side effects of radiation therapy were documented using the NCI Common Toxicity Criteria version 2.0.
- 6.12.4 Late toxicity monitoring: Beginning April 1, 2010, renal and GU toxicities will be evaluated and graded according to the NCI Common Terminology Criteria for Adverse Events (CTCAE) version 4.0. All appropriate treatment areas should have access to a copy of the CTCAE version 4.0. A copy of the CTCAE version 4.0 can be downloaded from the CTEP website ([http://ctep.cancer.gov/protocolDevelopment/electronic\\_applications/ctc.htm](http://ctep.cancer.gov/protocolDevelopment/electronic_applications/ctc.htm)). All other late ( $> 90$  days from RT start) side effects will be evaluated and graded according to the RTOG Late Radiation Morbidity Scoring Scale (Appendix IV).

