## **11.5 Criteria for Toxicity**

- 11.5.1 Acute toxicity monitoring:** Acute side effects ( $\leq 90$  days of treatment start) will be documented using the using the NCI Common Toxicity Criteria version 2.0.
- 11.5.2 Late toxicity monitoring:** Renal and GU toxicities will be evaluated and graded according to the NCI Common Toxicity Criteria version 2.0. All other late ( $> 90$  days from RT start) side effects will be evaluated and graded according to the RTOG Late Radiation Morbidity Scoring Scale (*Appendix IV*).

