**13.2.2** *Sample Size Derivation:* The sample size calculations will address the specific primary hypothesis that the maximally tolerated dose of 3D-CRT/IMRT delivered to patients with localized adenocarcinoma of the prostate will result in a hazard reduction of 23% in the mortality rate. Roach et al. identified four prognostic risk groups using independent predictors of death: combined Gleason score (*centrally reviewed*), T stage, and pathologic lymph node status. These groups were defined by observing the correlation between these factors and disease-specific survival. The five, ten and fifteen-year overall survival rates by risk group are presented in Table 1 below. Based on these risk groups, the probability of surviving in a five-year interval (1-5, 6-10, 11-15) is shown in Table 2. A preliminary analysis of RTOG 94-08, which is a two-arm study of endocrine therapy used as a cytoreductive and cytostatic agent prior to radiation therapy (RT) in locally confined adenocarcinoma of the prostate, showed a five-year overall survival rate of 74% for patients with clinical stage T1b-T2b, combined Gleason scores 2-6 and PSA  $< 20$  treated with radiation therapy alone. Forty-four percent of the men entered on RTOG 94-08 had a combined Gleason score between 2-6 and a PSA value  $\geq 10$  but  $< 20$  while 56% had a Gleason of 7 and PSA  $< 15$ . In light of these data, the survival estimates based on Roach et al. risk group two were used for the sample size calculations. The five and ten-year overall survival rates used were 80% and 48%, respectively. The hazard rates of the control arm are assumed to be constant within each five-year interval (1-5, 6-10, and 11-15) and they are 0.0446, 0.1022, and 0.1386, respectively. Five interim significance tests and a final test are planned. Early testing will employ a nominal significance level of 0.001 while a level of 0.020 will be used at the final analysis to preserve a 0.025 level for the study. Using Lakatos' method for time-dependent mortality rates, 715 deaths are required to detect a survival benefit translating into a hazard ratio ( $\Delta$ ) of 1.3 with 90% statistical power using a one-sided test at a level of significance of 0.025. This level of 0.025 is the same as a level of significance that would be required for a two-sided test of significance at 0.05 to show the experimental arm is better than the control arm. Using the projected hazard rates for each five-year interval, we will require a total sample size of 1410 to be accrued uniformly over five years with an additional eight years of follow-up. Guarding against an ineligibility or lack-of-data rate up to 8%, **the final targeted accrual for this study will be 1520 cases.** Some of the secondary endpoints that will be evaluated are PSA failure, disease-specific survival, and quality-adjusted survival. The planned PSA failure analysis after the 7th year is discussed in more detail in section 13.4.3.2. (9/18/03)

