#### **13.4 Analysis Plan (6/12/14)**

**13.4.1 *Statistical Methods:*** Gelman and Gaynor have shown that the Kaplan Meier method tends to overestimate cumulative failure probabilities for events with competing risks, such as time to PSA failure, disease-specific survival and time to distant metastases. Thus, the cumulative incidence approach will be used to estimate these endpoints as a function of time, since this approach specifically accounts for competing risks such as dying without a recurrence from prostate cancer. The distributions between the two arms will be compared by a method developed by Gray. Overall survival probabilities will be estimated by the usual Kaplan-Meier method. The survival distributions between the two arms will be compared using the log rank test. Factors associated with time to failure endpoints will be analyzed using the Cox regression model. Tumor control probability and normal tissue complication probability will be examined by categorical modeling techniques.

**13.4.2 *Interim Analysis to Monitor the Study Progress:*** Interim reports with statistical analyses will be prepared twice a year until the initial paper reporting the treatment results has been submitted.

In general, the interim reports will contain information about the patient accrual rate with a projected completion date for the accrual phase; data quality; compliance rate of treatment delivery with the distributions of important prognostic baseline variables; and the frequencies and severity of the toxicities by treatment arm. The interim reports will not contain the results from the treatment comparisons with respect to efficacy endpoints such as overall survival or PSA failure rate.

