**13.4.4 *Analysis For Reporting the Initial Treatment Results: (9/18/03)*** This major analysis will occur after each patient has been potentially followed for a minimum of eight years for the primary endpoint, overall survival, and for a minimum of five years for the secondary endpoint, PSA failure, unless the early stopping rule is satisfied. It will include tabulation of all cases entered and those excluded from the analyses with the reasons for such given; the distribution of the important prognostic baseline variables; and observed results with respect to all the above mentioned endpoints. The primary hypothesis for the study is whether the higher total dose of 3D-CRT/IMRT will improve overall survival. All eligible patients randomized will be included in the comparison and will be grouped by assigned treatment in the analysis. The primary hypothesis of MTD 3D-CRT/IMRT treatment benefit will be tested using the Cox proportional hazard model with the major stratification factors included as fixed covariates. Additional analyses of treatment effect will include modifying factors such as age, race, and other patient characteristics. These analyses will also use the Cox proportional hazards model. The treatment comparison of time to PSA failure and disease-specific survival will be analyzed in a similar fashion. The treatment comparison of 2+ grade toxicity rates will use the z-statistic for testing binomial proportions. Also, where feasible, treatment comparisons with respect to time to PSA failure and overall survival will be compared within each ethnic category. Secondary analyses of the primary and secondary endpoints will be performed using the available Gleason scores from central review. Comparison of the proportion of patients with ED at one year by treatment arm will be performed using a chi-square test. Other comparisons will be made for subsets defined by the dose to the penis bulb and by age (<70 vs.  $\geq 70$  years old) respectively. Quality of life change scores from pretreatment to one year will be compared between treatment arms using a t-test. Quality of life will be correlated with responses on the IIEF. The z-test will be used to compare between treatment arms the average quality-adjusted survival within the first five years. An area under the curve analysis will be performed to compare the bowel and bladder symptoms assessed using FACE over the first five years.

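### Late renal/GU toxicity is graded on two different scales from 1 April 2010, and late grade 2+ toxicity is compared by a crude binomial test that leans slightly against the high-dose arm if survival differs as designed

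*Protocol*

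**What the plan says.** Objective 2.2.3 is to "Determine the incidence of grade 2 or greater GU and GI acute and late toxicity in patients treated with each of the regimens", and Section 13.1.2 lists grade 2 or greater GU and GI toxicity as a secondary endpoint. The endpoint therefore includes late events, meaning those more than 90 days from the start of radiotherapy.

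On grading, Section 6.12.4 says: "Beginning April 1, 2010, renal and GU toxicities will be evaluated and graded according to the NCI Common Terminology Criteria for Adverse Events", version 4.0. Section 11.5.2, on the same late events, says: "Renal and GU toxicities will be evaluated and graded according to the NCI Common Toxicity Criteria version 2.0". It gives no date. Both sections put all other late effects, GI included, on the RTOG late morbidity scale.

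On analysis, Section 13.4.4 says: "The treatment comparison of 2+ grade toxicity rates will use the z-statistic for testing binomial proportions". It gives no time point and does not separate acute from late events. The same section fixes one year for erectile dysfunction and quality-of-life change, and five years for quality-adjusted survival and FACE. Section 13.4.3.2 has toxicity reported with the PSA analysis after year 7; the main analysis follows at year 13.

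Section 13.4.1 plans cumulative incidence with Gray's test for PSA failure, disease-specific survival and distant metastases because "this approach specifically accounts for competing risks such as dying without a recurrence from prostate cancer". Toxicity is not on that list.

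**The concern.** Toxicity is the harm side of a dose-escalation question, so both its definition and its comparison between arms need to be firm.

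The definition is not firm for late GU events. From 1 April 2010 a site following Section 11.5.2 and a site following Section 6.12.4 would use different scales. Even if the text is read as a dated switch, one patient's follow-up can span both scales, and no rule for combining them is given.

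The comparison uses a method suited to events observed over one fixed, complete window. Late toxicity is observed over unequal follow-up and cut short by death and loss. A crude proportion must either count an early death or loss as event-free or drop it, and neither uses the time at risk. The trial is designed on the hypothesis that Arm 2 patients live longer. If so, they have more time in which to record a late event, and the crude proportion in Arm 2 rises even when toxicity per year at risk is the same.

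**Working it through.** **Grading: the passages side by side.** The heading of Section 6.12 carries the amendment date 3/29/10. Appendix V, parts B and D, carries the same date and also names CTCAE version 4.0 from 1 April 2010. Section 11.5 has no such date. Both sections are current operative text, so a site can follow either.

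**Comparison: inputs from Section 13.2.2.** There are 1410 evaluable patients, taken as 705 per arm, with uniform accrual over 5 years plus 8 years of follow-up. For the control-arm death hazards by five-year interval, "they are 0.0446, 0.1022, and 0.1386, respectively". The hazard ratio is 1.3, so Arm 2 hazards are these divided by 1.3.

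**Reproducing the plan's own figures.** Control survival is exp(-5 × 0.0446) = 80.0% at 5 years and exp(-5 × 0.0446 - 5 × 0.1022) = 48.0% at 10 years. This matches the text: "The five and ten-year overall survival rates used were 80% and 48%, respectively". Expected deaths at years 4, 6, 8, 10, 12 and 13 come to 84, 185, 319, 477, 639 and 714, against the stated 85, 186, 320, 478, 640 and 715.

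**Exposure by arm.** At year 7 about 139 + 110 = 249 of 1410 have died (18%). At year 13 it is about 389 + 326, or 714 before rounding (51%). Survival is 48.0% against 56.9% at 10 years and 31.7% against 41.3% at 13 years.

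**Crude proportion when toxicity hazards are equal.** Let λ be the yearly hazard of a first late grade 2+ event, the same in both arms, and let S_a(t) be survival in arm a. For analysis at year T:

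P_a(T) = (1/5) ∫₀⁵ ∫₀^(T-u) λ e^(-λt) S_a(t) dt du

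With shift δ = P₂ - P₁ and SE = √(2 p̄(1 - p̄)/705), a two-sided 5% z-test rejects with probability about Φ(-1.96 + δ/SE) + Φ(-1.96 - δ/SE). The protocol states neither λ nor a significance level for toxicity. Both are assumptions here, and λ is varied from 2% to 5% per year.

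Example at λ = 3% and year 13: P₁ = 20.4%, P₂ = 21.7%, δ = 1.24 points, SE = 2.17 points and δ/SE = 0.57. Rejection is Φ(-1.39) + Φ(-2.53) = 8.8%.

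| λ per year | Year 7, constant: shift (points), rejection | Year 13, constant | Year 13, hazard stops at 5 years |
|---|---|---|---|
| 2% | 0.19, 5.2% | 0.89, 7.6% | 0.21, 5.2% |
| 3% | 0.28, 5.3% | 1.24, 8.8% | 0.31, 5.3% |
| 4% | 0.36, 5.4% | 1.55, 10.0% | 0.40, 5.5% |
| 5% | 0.43, 5.5% | 1.80, 11.2% | 0.48, 5.6% |

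The only late rates in the protocol that can anchor λ are the five-year actuarial grade 2 rates of about 10% (GU) and 11% (GI) in the single-institution series described in Section 1.1. A 10% rate gives λ = -ln(0.90)/5 = 2.1% per year. At year 13 the crude proportions are then 14.9% against 15.9% with 7.7% rejection if the hazard stays constant, and rejection is 5.2% if it stops at five years.

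**Acute toxicity.** By 0.25 years 1.1% of control and 0.9% of high-dose patients are expected to have died, so the binomial test is adequate there.

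**Would Gray's test suffice?** A simulation of 8,000 trials with the same inputs (equal toxicity hazards, year 13) gave 8.7% rejection for Gray's test at 3% per year, against 8.8% for the z-test. At 2.1% per year it gave 6.9% against 7.7%. Cumulative incidence itself depends on mortality, so Gray's test handles staggered entry and loss but does not remove the effect of differing survival.

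**The case against.** Several objections carry weight.

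- **Estimand.** If men on high dose live longer, more of them really do experience late toxicity. The proportion ever harmed is a legitimate quantity, and the z-test leans only relative to the toxicity rate while at risk. This stands, and it is why both quantities should be shown.
- **Size.** The shift is negligible at the first toxicity report and conditional at the last. It needs a survival difference, and it needs toxicity to keep accruing well past five years. A constant 5% per year implies 1 - exp(-0.65) = 48% actuarial toxicity by year 13, which nothing in the protocol supports. This stands.
- **What the SAP may hold.** A time point, a denominator or a rule for losses could be set there. That would answer part of the point, so their absence alone is no finding. But the protocol itself names the test, and the grading conflict is within the protocol.
- **Consistency with Section 13.4.1.** A reader might infer that Section 13.4.1 already adopts time-to-event methods to neutralise unequal survival between arms. It does not. It adopts cumulative incidence because Kaplan-Meier overestimates failure when deaths compete, and Gray's test would not remove the effect described here.
- **Grading.** Section 11.5.2 may simply not have been updated in 2010, so that a conforming edit is enough. That is plausible, but it still has to be made. A reader might also infer that two scales make the GU results uninterpretable. The documents do not support that: a switch on one calendar date falls on both concurrently randomised arms alike, and GI grading is unaffected.

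**Conclusion.** The point holds in two limited parts.

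The grading conflict needs no assumption. Sections 6.12.4 and 11.5.2 assign different scales to the same late renal/GU events from 1 April 2010, and a stated endpoint depends on them. The consequence is pooled absolute GU rates that are harder to read, not a biased comparison. Which scale should apply is not judged here.

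The crude test is a modest weakness in a secondary endpoint and does not touch the overall survival result. It rests on the design hazard ratio of 1.3 being true, on equal toxicity hazards, and on the assumed λ and significance level. Under those conditions the lean is always towards overstating harm in Arm 2. It is effectively nil at year 7 and matters at year 13 only if late toxicity keeps accruing. A reader might infer a serious bias throughout, with half the patients dead at both reports. The plan's own hazards put deaths at 18% at year 7 and 51% only at year 13. Loss to follow-up is a separate weakness of the crude proportion that does not depend on any survival difference, but the documents give no figure with which to size it.

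**What to change.** 1. Reconcile Sections 6.12.4 and 11.5.2, and state which scale defines the grade 2 or greater late GU endpoint. If there is a dated switch, add a sensitivity analysis that censors GU events at 1 April 2010 so that one scale applies throughout.
2. In Section 13.4.4, keep the binomial z-test for acute toxicity only.
3. For late GI and late GU separately, analyse time to first recorded grade 2 or greater event by log-rank test and Cox model on the cause-specific hazard, stratified by Gleason/PSA group and radiation modality, censoring at death or last toxicity assessment. Toxicity is evaluated at every scheduled visit, but no section says that onset dates are recorded. If they are not, use the visit date.
4. Display cumulative incidence by arm with death as a competing event. Do not rely on Gray's test alone to deal with differential mortality.

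The cost is protocol wording and modest programming. The tested quantity becomes the toxicity rate while at risk rather than the proportion ever affected, so the cumulative incidence should be reported beside it.

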**13.4.5 *Revised Interim Futility Analysis Plan (6/12/14)***

As described in Section 13.4.3.1, there will be five interim analyses of the primary hypotheses, at the increments of the requisite events for definitive analysis indicated. The interim futility analysis plan calls for evaluation of whether conditional power falls below 10% at each of those interim analyses. The following revised futility monitoring plan will be carried out for remaining interim analyses.

Interim futility analysis will be based on the lower inefficacy boundary (LIB) rule of Freidlin, Korn, and Gray. This rule provides the opportunity to terminate early for evidence that the experimental arm will not prove superior, but protects against aggressive early termination for treatment effect sizes smaller than planned. For implementation, we chose the LIB40 rule as suggested for a moderately aggressive futility stopping criterion in late follow-up. Note that futility monitoring does not apply before the time to commence such monitoring derived from the formula given in Freidlin, Korn and Gray, and in any case, those interim analyses have already been completed.

The following table summarizes the interim futility monitoring schedule:

| Analysis  | Prop. Total events | Cumulative Total Events (Both Arms) | Futility boundary: stop if |       |                    |
|-----------|--------------------|-------------------------------------|----------------------------|-------|--------------------|
|           |                    |                                     | Z<                         | P>    | HR (Exp/Control) > |
| Interim 1 | 0.12               | 85                                  | NA                         | NA    | NA                 |
| Interim 2 | 0.26               | 186                                 | NA                         | NA    | NA                 |
| Interim 3 | 0.45               | 320                                 | 0.126                      | 0.450 | 0.986              |
| Interim 4 | 0.67               | 478                                 | 0.564                      | 0.286 | 0.950              |
| Interim 5 | 0.90               | 640                                 | 1.124                      | 0.131 | 0.915              |
| final     | 1.00               | 715                                 | -                          | -     | -                  |

### 13.5 Inclusion of Minorities

In conformance with the national Institutes of Health (NIH) Revitalization Act of 1993 with regard to inclusion of women and minorities in clinical research, we address this issue here, as we will also analyze treatment differences in this male cohort by ethnicity. Based on previous RTOG prostate protocol data the minority enrollment for this study is expected as follows:

| Ethnic Group                              | Number      | Percent (%) |
|-------------------------------------------|-------------|-------------|
| American Indian or Alaskan Native         | 3           | 0.2         |
| Asian                                     | 8           | 0.5         |
| Black or African American                 | 228         | 15.0        |
| Hispanic or Latino                        | 46          | 3.0         |
| Native Hawaiian or other Pacific Islander | 4           | 0.3         |
| White                                     | 1216        | 80.0        |
| Other/Unknown                             | 15          | 1.0         |
| Total                              | 1520 | 100  |

Obviously with 80% of the available sample being white, univariate comparisons by treatment will not yield sufficient power in most cases. We will, however, also include the ethnicity variable in all regressions including the Cox model.

